Reportedly, regular physical activity and fatigue can affect blood biomarker levels, including inflammatory markers [26] and oxidative stress [27]. Evidence from randomized controlled trials (RCTs) has indicated an effect of physical activity in patients with cancer on the levels of circulating growth factors and cytokines (eg, interleukin 6 and tumor necrosis factor alpha) [28,29] and suggests that physical activity might markedly alter the frequency and functional competence of immune cell subsets of the innate immune system (eg, neutrophils, monocytes, and natural killer cells) [30,31]. Concerning the oxidative stress, an excessive accumulation of oxidative stress in cells has been shown to induce marked cellular and molecular damages and likely plays an important role in carcinogenesis, tumor promotion, and breast cancer recurrence and metastasis [32-34]. Moreover, plasma antioxidant defenses seem to be lower in women with breast cancer [34]. On the contrary, physical activity programs have shown to decrease the oxidative stress in patients with chronic diseases other than cancer, in particular through the improvement of enzymatic antioxidant defenses [27,35].

The Advanced stage Breast cancer and Lifestyle Exercise (ABLE) Trial was designed to address the gaps in the current literature. The primary aim is to determine the feasibility of an unsupervised and personalized physical activity intervention in patients with metastatic breast cancer. The secondary aims are to investigate (1) how the physical activity intervention changes the total global physical activity, sedentary time, and physical fitness; (2) how the physical activity intervention changes patient-reported outcomes, including the quality of life and fatigue; (3) how the physical activity intervention changes patients’ anthropometric measurements and body composition; (4) the barriers and facilitators of the adherence to a physical activity program; and (5) whether the physical activity intervention affects the oxidative stress and inflammation as biomarkers of the tumor progression.

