### Study Population

The inclusion criteria for this study are as follows: (1) female; (2) aged 18-78 years; (3) newly diagnosed with primary or secondary metastatic breast cancer histologically confirmed (ie, within the last 3 months) and treated in a cancer center by chemotherapy or radiotherapy or hormonal therapy or targeted therapy; (4) Eastern Cooperative Oncology Group Performance status <2; (5) able to speak and understand French and able to complete questionnaires and follow instructions in French; and (6) valid health insurance affiliation. For patients willing to participate in the study, confirmation from their treating oncologist of no contraindications to physical activity is required.

The exclusion criteria for this study are as follows: untreated brain metastases; pregnancy; and contraindications to physical activity (eg, uncontrolled hypertension, cardiac disease). All patients must sign an informed consent form.

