#### Demographic and Clinical Data

Demographic and clinical data, including date of birth, age at diagnosis, living situation, employment status, hormonal status, tumor histology, personal history of breast cancer, sites of metastases, and current treatment, are collected at the baseline. The Response Evaluation Criteria In Solid Tumors (RECIST) is used to assess the tumor progression between the diagnosis and the end of the physical activity program [36]. All clinical data are extracted from patients’ electronic medical records.

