#### Biological Data

A 7-mL blood sample is collected at the baseline (D1) and at the end of the study after 6 months (M6). The sample is centrifuged within half an hour after drawing and kept at 4°C before and during centrifugation. The plasma is distributed into cryotube aliquots of 1 mL and buffy coat in a single 1-mL cryotube; these cryotubes are frozen and stored at −80°C at the center and used for the analyses of oxidative stress and antioxidant biomarkers. Superoxide dismutase, catalase, glutathione peroxidase enzymatic activities, and markers of DNA oxidation (8-hydroxy-2'-deoxyguanosine), prostaglandins oxidation (8-Iso Prostaglandin F_2α__)_ are measured in the plasma [50]. Furthermore, levels of circulating growth factors, cytokines, neutrophils, monocytes, and natural killer cells are assessed as previously described [51].

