#### Statistical Methods

Patients’ characteristics will be described at D1 and M6 using the mean and SD for quantitative data, frequency, and percentage for qualitative data.

The primary outcome to assess the feasibility of the study will be the proportion of patients achieving the physical activity recommendations corresponding to 150 minutes per week of moderate physical activity evaluated by the IPAQ score during the last week of the study. In addition, we will estimate the proportion of patients who agreed to participate in the ABLE Trial among eligible patients. The reasons for refusal will be documented and described as well.

The secondary outcomes to assess will be the evolution of physical activity, anthropometric, physical fitness, psychological, and biological variables between the initiation (D1) and the completion (M6) of the physical activity intervention using Wilcoxon signed-rank tests. In addition, the level of physical activity according to biological, psychological, and clinical outcomes adjusted on potential confounders, including age, treatment, and number of visits, will be explored using multiple linear regressions. Moreover, the level of oxidative stress will be correlated to the RECIST criteria. Data on barriers and facilitators of the adherence to a physical activity program from D1 to M6 will be compared by Mac Nemar tests. All statistical analyses will be performed using SAS software (version 9.4. SAS Institute Inc, Cary, NC, USA).

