## Discussion

### Principal Findings

Given the beneficial effects of physical activity in localized breast cancer, the ABLE Trial is the first European study to propose a physical activity intervention for patients with metastatic cancer that will obtain preliminary data on biological, functional, psychological, and clinical outcomes and identify the determinants of physical activity. In addition, the use of wearable activity trackers in the ABLE Trial strengthens its novelty. Although wearable activity trackers are comparable to pedometers in some aspects, they are more effective for behavioral modification [52] because the Health Mate app and the wearable activity tracker provide more detailed data on the physical activity performed over time. These types of devices are emerging in the health care field and are being shown to help motivate people to increase their physical activity level and facilitate them to reach a personal or recommended goal because of the feedback received in real time (eg, steps) [23-25]. International recommendations for patients with cancer are to practice 30 minutes of moderate physical activity per day at least 5 times a week [53]. The number of steps per day is more easily comprehensible for individuals to achieve these physical activity recommendations. For adults with health impairment, 5000-7000 steps per day might be a more appropriate target than the target of 10,000 steps per day recommended for healthy people [54]. Indeed, walking is feasible at no charge and practiced by the majority of people. In the ABLE Trial, the recommended number of steps is individualized to each patient because research has suggested that a small goal is more effective and easier to achieve than a higher activity goal. In addition, it is important to increase these physical activity targets gradually [24].

The links between the level of physical activity and the biological mechanisms involved in the tumor progression have never been studied in patients with metastatic breast cancer. A study of the oxidative stress in this population might help identify potential new biomarkers associated with physical activity and tumor progression.

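### The planned correlation of oxidative stress with RECIST names no adjustment for treatment, which may influence both

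*Protocol article*

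**What the plan says.** In the protocol article, Statistical Methods, the analysis is one clause: "the level of oxidative stress will be correlated to the RECIST criteria". No coefficient, covariate or stratification is given. The sentence before it covers regressions that relate physical activity to biological, psychological and clinical outcomes. Those are "adjusted on potential confounders, including age, treatment, and number of visits, will be explored using multiple linear regressions".

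The Study Population section admits women "treated in a cancer center by chemotherapy or radiotherapy or hormonal therapy or targeted therapy", with no expected shares. RECIST "is used to assess the tumor progression between the diagnosis and the end of the physical activity program" (Demographic and Clinical Data). Under Biological Data, blood is drawn at D1 and M6. Treatment is recorded: "sites of metastases, and current treatment, are collected at the baseline", and Table 1 lists current treatment at both D1 and M6.

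The analysis serves secondary aim 5 in the Introduction, which asks "whether the physical activity intervention affects the oxidative stress and inflammation as biomarkers of the tumor progression". Principal Findings adds that studying oxidative stress in this population "might help identify potential new biomarkers associated with physical activity and tumor progression".

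**The concern.** RECIST records tumor change over a period in which these women are being treated, and the cohort mixes four kinds of treatment. If treatment classes differ in tumor response and also in their effect on oxidative stress, pooling them creates a correlation between marker and RECIST even when the two are unrelated within every class. If the two treatment effects run in opposite directions, pooling could instead hide a true link.

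The protocol itself regards treatment as a potential confounder of biological and clinical outcomes, yet names no adjustment in the next sentence, where a biological measure is set against a measure of tumor response. This is the only listed analysis that relates oxidative stress directly to tumor progression. What is at stake is how that biomarker result is read, and whether a lead produced by treatment mix is carried into the multicenter trial that this study is meant to inform.

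**Working it through.** The plan states no coefficient, significance level, power or effect size for this correlation, so there is no figure to reproduce. The check shows how large the distortion could be and whether adjustment removes it.

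**From the documents:** planned recruitment of 60 (Sample Size); four treatment modalities pooled (Study Population); treatment collected (Demographic and Clinical Data, Table 1).

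**Assumed, because the documents give no values:** treatment share, response rates by class, marker shift by class, a two-sided 5% test, and complete data on all 60.

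**Mechanism.** Let a share p of women be on one treatment class. Let that class shift both the marker and an underlying response scale by d SD, with no link between them within a class. The pooled correlation on the underlying scale is

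r = p(1 − p)d² / [1 + p(1 − p)d²].

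- p = 0.5, d = 0.5: 0.0625 / 1.0625 = 0.059
- p = 0.5, d = 0.8: 0.16 / 1.16 = 0.138
- p = 0.5, d = 1.0: 0.25 / 1.25 = 0.200

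All of this comes from treatment mix.

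**Simulation A: response rates assumed directly.** n = 60, half in each class, 4000 runs. Probabilities of progression / stable / partial / complete response are 0.15/0.35/0.40/0.10 in one class and 0.30/0.50/0.18/0.02 in the other. Objective response is therefore 0.40 + 0.10 = 50% against 0.18 + 0.02 = 20%. There is no link between marker and response within a class.

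| Marker shift (SD) | Crude Spearman, significant | Ranks centred within class |
|---|---|---|
| 0.5 | about 9% | about 5% |
| 0.8 | about 15% | about 5% |
| 1.0 | 19-20% | about 5% |

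The mean crude correlation runs from about 0.07 to 0.14. Repeat runs agree to within about one percentage point.

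**Simulation B: equal shift of d SD on both variables.** n = 60, 3000 runs, four-category RECIST.

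| d | Mean rho, share 30% / 50% | Crude, significant | Adjusted, significant |
|---|---|---|---|
| 0.3 | 0.02 / 0.02 | 5% / 6% | about 5% |
| 0.5 | 0.05 / 0.06 | 7% / 7% | about 5% |
| 0.8 | 0.11 / 0.13 | 13% / 16% | about 5% |
| 1.0 | 0.16 / 0.19 | 23% / 33% | about 5% |

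Across the simulated settings the adjusted rate stays between 4.6% and 5.7%.

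**Reading.** The inflation is slight when both shifts are 0.5 SD or less and grows quickly from about 0.8 SD. Rates are per marker; Biological Data lists five oxidative stress or antioxidant markers. With fewer than 60 complete pairs the inflation would be smaller. The adjusted rate of about 5% assumes that the recorded class captures the whole treatment effect.

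**The case against.** The strongest reply is that the sentence is silent on adjustment and does not rule it out. A condensed article may leave the coefficient, the covariates and the visit to the full plan. That is right for the visit: not saying whether the D1 or the M6 sample is meant is no fault here. It is only partly right for adjustment, because adjacent sentences differ. One names treatment as a confounder and the next, where treatment is at least as relevant, does not.

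Second, a reader might infer that treatment does drive both variables, with chemotherapy as the cause. The documents do not support this. Nowhere do they say that treatment changes oxidative stress or that RECIST response differs by treatment type, and they give no treatment shares. Only "may influence both" can be defended, and every input to the simulations is an assumption.

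Third, the trial is about feasibility, and Principal Findings uses tentative language about biomarkers. A crude association can prompt a hypothesis, and no primary result or decision rests on this one. That stands, and it limits the harm to the biomarker interpretation.

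Fourth, it is tempting to say that using the D1 level would show whether the marker precedes progression. It would not. RECIST runs from diagnosis, and the inclusion criteria allow diagnosis up to 3 months before entry, so the D1 sample can fall inside the RECIST window.

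**Conclusion.** The point holds in a limited form. As described, the correlation cannot separate treatment mix from a link between oxidative stress and progression, and the protocol's own confounder list names the variable needed to do so. In Simulation A, false positives at n = 60 rise from 5% to about 9-20% per marker, and adjustment restores about 5%. These figures illustrate the possible size; they are not estimates for this trial. Below about 0.5 SD on both variables the problem is minor. The documents do not show that a treatment effect on the marker exists, so it would be wrong to conclude that the correlation will be spurious. The feasibility outcome is unaffected.

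**What to change.** Replace the sentence with one along these lines: the association between oxidative stress markers and RECIST category will be explored by partial rank correlation (or ordinal regression of the RECIST category), adjusted for treatment class. Set the D1-to-M6 marker change against RECIST, report it as an association only, and make no claim that the D1 level precedes progression. Define the treatment classes before analysis. If the sponsor prefers to keep the crude correlation, label it descriptive and do not use it to support a biomarker statement.

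The cost is one sentence and one or two degrees of freedom. Treatment and both blood samples are already collected. One limit remains: adjusting for the class at D1 does not capture later treatment changes. Table 1 also records treatment at M6, so the number of women who changed class can be reported alongside.

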## Results

The recruitment and enrollment in this single-arm feasibility trial started in October 2016. A follow-up was completed in January 2018. Data analyses began in February 2018 and will be completed in October 2018. All results are expected to be available by the end of 2018.

## Discussion

### Principal Findings

Given the beneficial effects of physical activity in localized breast cancer, the ABLE Trial is the first European study to propose a physical activity intervention for patients with metastatic cancer that will obtain preliminary data on biological, functional, psychological, and clinical outcomes and identify the determinants of physical activity. In addition, the use of wearable activity trackers in the ABLE Trial strengthens its novelty. Although wearable activity trackers are comparable to pedometers in some aspects, they are more effective for behavioral modification [52] because the Health Mate app and the wearable activity tracker provide more detailed data on the physical activity performed over time. These types of devices are emerging in the health care field and are being shown to help motivate people to increase their physical activity level and facilitate them to reach a personal or recommended goal because of the feedback received in real time (eg, steps) [23-25]. International recommendations for patients with cancer are to practice 30 minutes of moderate physical activity per day at least 5 times a week [53]. The number of steps per day is more easily comprehensible for individuals to achieve these physical activity recommendations. For adults with health impairment, 5000-7000 steps per day might be a more appropriate target than the target of 10,000 steps per day recommended for healthy people [54]. Indeed, walking is feasible at no charge and practiced by the majority of people. In the ABLE Trial, the recommended number of steps is individualized to each patient because research has suggested that a small goal is more effective and easier to achieve than a higher activity goal. In addition, it is important to increase these physical activity targets gradually [24].

The links between the level of physical activity and the biological mechanisms involved in the tumor progression have never been studied in patients with metastatic breast cancer. A study of the oxidative stress in this population might help identify potential new biomarkers associated with physical activity and tumor progression.

Of note, some limitations are acknowledged in the ABLE Trial. First, the sample size is limited but is sufficient to test the feasibility of the intervention. Second, the device used in the study has not been validated but uses the same algorithm as Nokia Pulse that has been validated by comparing this tracker with the OptoGait system for laboratory and ActivPAL for free-living conditions [20]. Finally, the test-retest reliability for Nokia Pulse was excellent with an intraclass correlation coefficient >0.90.

The results of this trial will provide quantitative and qualitative outcomes that will help design a future multicenter RCT on a physical training intervention in patients with metastatic breast cancer. Given the paucity of data in this population of patients and the potential for measurable health benefits to them, in many domains, this trial will provide new data that will be relevant in assessing the feasibility and acceptability of a larger-scale trial for this previously underinvestigated population.

### Ethics and Dissemination

The study protocol was approved by the French ethics committee (Comité de protection des personnes Sud-Est IV), and the study database was declared to the National Commission for Data Protection and Liberties (CNIL; reference number: 1994192).

## Abbreviations

6MWT: 6-minute walk test
ABLE: Advanced stage Breast cancer Lifestyle and Exercise
D1: day one
IPAQ: International Physical Activity Questionnaire
M6: end of 6 months
MET: metabolic equivalent of task
RCT: randomized controlled trial
SMS: Short Message Service
